#### *Structural brain adaptations*

Differences in connectivity between pre-test and post-test assessment, both within and between groups (i.e. type of prosthesis), will be analysed by means of structural equation modelling. This analysis allows to investigate the causal relationships between brain structure and performance indicators while controlling for confounding factors. The factors time since amputation, side of amputation, amputation level, time using prosthesis, previously used prosthesis, age, sex, Mini-Mental State Examination score, and level of education will be accounted for. Statistical significance level will be set at 5%.

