### 3. Justification for the design of the clinical investigation

A first clinical study, led by the VUB, has been conducted with the LUNARIS® Demonstrator. The complete protocol (B.U.N. 143201526629) has been approved by the medical Ethics Committee of the University Hospital of the VUB.

In this study, forty-two participants completed the protocol assessing performance and functional mobility with their current prosthesis and the LUNARIS® Demonstrator. Subjective measures indicated the added value of this device, while overall task performance and intensity of effort did not differ between the LUNARIS® Demonstrator and the current prosthesis. The familiarisation time only lasted between one and two hours, which was not enough to obtain significant results between the LUNARIS® Demonstrator and the current prosthesis of the user [1].

In addition, a systematic review about therapeutic benefits of lower limb prosthesis was performed in 2021. It could be concluded that no studies investigating the long-term therapeutic benefits of performing daily activities with passive, quasi-passive and active ankle-foot prostheses in people with unilateral lower-limb amputation were found, highlighting a gap in the literature [2].

Lastly, further investigations (B.U.N. 143201526629 - Amendment) unravelling both acute and more prolonged adaptations were conducted to evaluate the LUNARIS® Demonstrator. This study revealed a potential long-term benefit of recovering a gait pattern of able-bodied persons after a few months of familiarisation. We hypothesised that it might be a consequence of the high flexibility of the LUNARIS® Demonstrator [3].

As a result, this study aims to demonstrate that doing the rehabilitation with the LUNARIS® may allow the user to recover a gait pattern closer to the one of able-bodied person and that brain plasticity will be less impacted when walking with the LUNARIS® than with another rigid prosthetic device. Studying the effect of the LUNARIS® during rehabilitation could be a great opportunity to investigate the rehabilitation with an articulated ankle prosthesis and the long term benefits of the LUNARIS®.

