### d) Primary and secondary hypotheses

The different hypotheses (H) are:

**H1** We hypothesise that people walking with the passive prosthesis (LUNARIS®) will be able to cover significantly more distance (i.e.,  $> 35$ m) during 6-min walking compared to people walking with their current prosthetic device [4][5]. Secondly, we expect that wearing the LUNARIS® will improve postural stability and improve movement patterns after 12 weeks compared to walking with the current ankle prosthesis [6][7][8]. Thirdly, we noticed based on anecdotal evidence that people walking with the LUNARIS® are able to descend stairs more naturally, like able-bodied people. We hypothesise that doing the rehabilitation with the LUNARIS® will help people descending stairs without the need of rolling over the edge of a step, and as a consequence, will reduce the number of falls.

**H2** Based on my literature review on brain neuroplasticity after a lower limb amputation, we hypothesise to discover differences in structural whole-brain networks between participants with the LUNARIS® and current prosthesis after 12 weeks. We assume that these differences in structural networks will be less pronounced among people wearing the LUNARIS® compared to people wearing the current

prostheses [9]. Furthermore, we expect that these disparities in brain structural connectivity will translate into a change in performance on the physical tests.

e) Risks and anticipated adverse device effects that are to be assessed

To date, no device deficiencies have been reported with the LUNARIS®. We are not yet able to give a concise summary of device deficiencies and thus not able to report any deficiency that might have led to a serious adverse event if appropriate action had not been taken, intervention had not occurred, or circumstances had been less fortunate.

The Risk Management File is attached to this document.

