### *Able-bodied subjects:*

There is only one measurement moment for able-bodied subjects which will be divided into two days.

**Day 1:** the subject will be expected at the radiology department at UZ Brussel. Here, a non-invasive brain scan will be taken under the supervision of [name]. [name] (department head of Radiology). This measurement moment will take approximately 60 minutes.

**Day 2:** the subject will be expected at Axiles Bionics for a series of non-invasive tests. This measurement moment will take approximately 60 minutes.

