### b) Descriptive statistics of baseline data

#### *Functional performance testing*

A mixed model will be constructed enabling within and between group (i.e., type of prosthesis) comparison of balance performance and accounting for baseline covariates. If residuals are not normally distributed, required adaptations to the data or model will be performed. To correct for multiple comparisons, suited corrections will be applied. The factors age, time since amputation, side of amputation, level of amputation, time using prosthesis, previously used prosthesis will be accounted for. Statistical significance level will be set at 5%.

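### Section 7 b compares only types of prosthesis, so it never tests whether gait with LUNARIS comes closer to able-bodied gait, and H2 names no reference for smaller brain change

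*Protocol*

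**What the plan says.** **The aim.** Section 3, repeated in section 4 a, says that rehabilitation with LUNARIS "may allow the user to recover a gait pattern closer to the one of able-bodied person and that brain plasticity will be less impacted" than with a rigid device. The gait part is stated relative to able-bodied people. The brain part is stated relative to a rigid prosthesis.

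**The able-bodied group.** Sections 5 c and 7 e include 20 matched able-bodied people for comparison, and the sample size calculation counts three groups. Section 7 f says their measurements are needed to see similarities to and differences from LUNARIS. Section 7 a puts everyone enrolled into the analysis. Section 6.4 a adds: "There is only one measurement moment for able-bodied subjects which will be divided into two days".

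**The analysis.** For function, section 7 b says: "A mixed model will be constructed enabling within and between group (i.e., type of prosthesis) comparison of balance performance". For the brain, the outcome is "Differences in connectivity between pre-test and post-test assessment, both within and between groups (i.e. type of prosthesis"), analysed by structural equation modelling.

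**The hypothesis.** H2 in section 5 d begins: "we hypothesise to discover differences in structural whole-brain networks between participants with the LUNARIS® and current prosthesis after 12 weeks". It continues: "We assume that these differences in structural networks will be less pronounced among people wearing the LUNARIS", compared with current prostheses.

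**The concern.** The gait aim is about closeness to a third group, but the contrast fixed in section 7 b is between two types of prosthesis. For walking distance this would not matter, because more is better. Section 6.1 e, however, evaluates gait through coordination between joints or segments (continuous relative phase). Only the variability of gait is given an unfavourable direction there. For the coordination pattern itself, a shift up or down is good or bad only in relation to able-bodied values.

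The brain analysis has a related gap. Week 0 is the start of rehabilitation, which comes after the amputation, so the networks may already have changed by the first scan. Change from week 0 to week 24 may then be recovery or further drift, and the plan gives no way to tell which.

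At stake is the interpretation of the secondary gait and brain results. Twenty people would be scanned and tested without any specified analysis of the gait aim that justifies including them.

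**Working it through.** The core is settled by setting the sections side by side. The protocol gives no SD, effect size or sample size for gait coordination or connectivity. Its figure of 40 participants with amputation concerns walking distance and does not bear on this point.

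**1. Can the able-bodied group enter the analyses in section 7 b?**

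| Element of 7 b | Functional model | Brain model |
|---|---|---|
| Group factor | Type of prosthesis: undefined for able-bodied people | Same |
| Outcome | Within-group and between-group comparison; able-bodied people measured once | Pre-to-post change; cannot be formed from one scan |
| Listed covariates that exist only after amputation | 5 of 6 (all but age) | 5 of 9 (all but age, sex, Mini-Mental State score, education) |

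As written, the able-bodied group fits neither model, although section 7 a includes everyone enrolled.

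**2. Does the prosthesis contrast tell closer from farther?** Assumed for illustration: a coordination measure with able-bodied mean 0, SD 1 in every group, 20 per arm, an arm difference of 0.9 SD, and a two-sided 5% z test with known variance.

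- Standard error of the arm difference: √(2/20) = 0.316.
- Standardised difference: 0.9/0.316 = 2.846.
- Probability of rejection: Φ(2.846 − 1.96) = Φ(0.886) ≈ 0.81.

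This depends only on the size of the arm difference. Simulation with 20,000 repetitions per row agrees:

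| LUNARIS mean | Comparator mean | True position of LUNARIS | Rejection |
|---|---|---|---|
| −0.3 | −1.2 | 0.9 SD closer to able-bodied | 0.804 |
| −1.2 | −0.3 | 0.9 SD farther | 0.814 |
| 0.45 | −0.45 | Equally far, opposite side | 0.815 |
| 1.2 | 0.3 | 0.9 SD farther, overshooting | 0.811 |

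The sign of the contrast does not settle it either. Rows 1 and 4 both have a difference of +0.9, yet LUNARIS is closer in one and farther in the other.

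**3. Does a deviation score tell them apart?** For a normal measure with mean μ and SD 1, the mean absolute deviation from 0 is √(2/π)·exp(−μ²/2) + μ·(1 − 2Φ(−μ)), for μ ≥ 0 (the sign of μ does not matter). Its variance is μ² + 1 minus that mean squared.

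- |μ| = 0.3: mean 0.834, variance 0.395.
- |μ| = 0.45: mean 0.877.
- |μ| = 1.2: mean 1.312, variance 0.718.

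LUNARIS minus comparator is therefore −0.48 in row 1, +0.48 in rows 2 and 4, and 0 in row 3, so the score separates the cases. It costs power. In row 1 the standard error is √((0.395 + 0.718)/20) = 0.236, the ratio is 0.479/0.236 = 2.03, and power is about Φ(2.03 − 1.96) = 0.53, against 0.81 for the raw contrast. This treats the able-bodied mean and SD as known.

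**4. Is H2 well defined?** Its first sentence concerns a difference between the arms. Its second says these differences are smaller in one arm, which a between-arm difference cannot be. If the intended quantity is change from week 0 to week 24, a smaller change fits both less harm and less recovery.

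**The case against.** **The objectives already match the analysis.** RO.1.3 asks whether the type of prosthesis changes the movement pattern, and RO.2 asks about network changes related to the type of prosthesis. Section 7 b addresses both. This stands, and a reader who infers that these objectives cannot be answered goes too far. What is not addressed is the stronger gait aim in sections 3 and 4 a.

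**The brain aim is not stated against able-bodied people.** Correct. A reader might infer an aim of brain networks closer to able-bodied ones, but the stated comparator is a rigid prosthesis. The able-bodied reference is proposed here as one way to give H2 a meaning.

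**Directions are given.** A reader might infer that a difference of either sign could be claimed as benefit. The text does not support that in general: H2 expects smaller differences with LUNARIS, section 6.1 e marks high gait variability as unfavourable, and H1 is directional. The ambiguity is confined to coordination measures other than variability and to what a smaller connectivity change means.

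**A non-significant comparison with able-bodied people might be read as similarity.** Section 7 f speaks of observing similarities, but no section commits to that reading, so it is not part of this point.

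**An analysis plan may supply the detail.** The comparison is announced in sections 5 c, 7 e and 7 f, and a separate plan could define it. However, section 7 b does not leave the contrast open. It fixes group as type of prosthesis and lists covariates to match.

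**Conclusion.** The point holds for gait coordination and, more narrowly, for the wording of H2. Section 7 b fixes a contrast that cannot show whether LUNARIS users come closer to able-bodied gait, and it gives the 20 able-bodied participants no analytic role. In the illustration the planned contrast rejects with a probability of about 0.81 whether LUNARIS is closer, farther or equally far on the other side. That figure rests on the assumed 0.9 SD difference, equal SDs and 20 per arm. The conclusion does not, because the contrast depends only on the arm difference and not on where able-bodied people lie.

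The 6-minute walk distance, H1, and RO.1.3 and RO.2 as worded are unaffected. This is a low-cost improvement to secondary analyses, not a threat to the primary result.

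**What to change.** - **Gait, section 7 b:** add a between-arm comparison at week 24 of each participant's absolute deviation from the able-bodied mean, in able-bodied SD units. Use a small pre-named set of coordination measures and state the direction: smaller with LUNARIS.
- **Connectivity, section 7 b:** add the same deviation on a few pre-named summary measures, adjusted for the week-0 deviation. Keep the set small. The eight regions in section 6.1 e give 8 × 7/2 = 28 pairwise connections, and a covariance matrix from 20 people has rank at most 19, so a multivariate distance over all of them cannot be computed without reducing the dimension.
- **H2, section 5 d:** reword it to name that reference, so that it predicts a smaller deviation from able-bodied values at week 24 with LUNARIS.
- **Covariates:** restrict the amputation and prosthesis factors to models containing amputees only. The comparisons proposed here are of that kind.

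**Cost:** wording in two sections and some extra analysis, with no new data. There are two downsides. A reference from 20 people is imprecise, so its uncertainty must be carried into the interval, for example by resampling all three groups in a bootstrap. The deviation score also has less power than the raw contrast (about 0.53 against 0.81 in the example, before allowing for that imprecision), so it should be reported with its interval as a secondary result beside the planned prosthesis contrast.

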##### Protocol:

Figure 2 provides a visualisation of the investigation workflow.

[figure not shown]

Figure 2: Overview clinical trial. MRI: Magnetic Resonance Imaging, PEQ: Prosthetic Evaluation Questionnaire, ADL: Activities of Daily Living

The clinical investigation will comprise 4 test days for participants with a lower limb amputation and 2 days for the control group of able-bodied individuals.

The able-bodied individuals will undergo an MRI-scan at the University hospital Brussels (dpt. Radiology and Magnetic Resonance) and then perform functional performance tests.

Participants with a lower limb amputation will start the clinical investigation upon the start of their rehabilitation. At week 0, when initiating the rehabilitation, participants will undergo a baseline MRI-scan at the University hospital Brussels (dpt. Radiology and Magnetic Resonance). Then, they will be allocated to the one of the treatment arms (LUNARIS® or the SACH® foot) and will conduct their rehabilitation to learn walking with a prosthesis. At the end of the rehabilitation, after 12 weeks, participants will perform baseline functional performance tests, fill out the prosthetic evaluation questionnaire (PEQ) measuring quality of life [11] and fill out the Mini-Mental State Examination to account for cognitive impairments and onset of Alzheimer's Disease [12]. Between weeks 12 and 24 of the clinical investigation (i.e. intervention period), participants will perform their daily activities with the allocated prosthesis. During this 12-week period, trying out new prosthetic devices will be allowed within the group of individuals wearing the SACH® foot as this is considered the usual care. At the end of this period (after week 24), post-test assessment will take place and participants will undergo the same MRI and functional performance tests as during the baseline assessments to evaluate the changes that occurred. Additionally, the participant will be asked to fill out the Quebec User Evaluation of Satisfaction with assistive Technology (QUEST 2.0) to assess prosthetic satisfaction [25-27]. The 12-week intervention period is chosen based on a study examining the effect of 12 weeks balance training in healthy and older adults on neuroplasticity and on the accommodation time to walking with a new prosthesis [13][14][15].

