## 6.4. Procedures

### a) Description of all clinical investigation-related procedures that subjects undergo during the clinical investigation

*Lower-limb amputees:*

There are three measurement moments for lower-limb amputees which will be divided into four days.

**Day 1:** the subject will be expected at the radiology department at UZ Brussel. Here, a non-invasive brain scan will be taken under the supervision of [name]. [name] (department head of Radiology). This measurement moment will take approximately 60 minutes.

**After 12 weeks:** the subject will be expected at Axiles Bionics for a series of non-invasive tests. This measurement moment will take approximately 120 minutes.

**After 24 weeks:** this measurement moment will be divided into two days. The subject will be expected on day 1 at the radiology department at UZ Brussel. Here, the same brain scan will be taken as described in measurement moment 1. This measurement moment will take about 60 minutes. On day 2, the subject will be expected at Axiles Bionics for a series of non-invasive tests as described in measurement moment 2. This measurement moment will take about 120 minutes.

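### The structural equation model for brain and performance is described as causal, but this design can support only an adjusted association without direction

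*Protocol*

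**What the plan says.** Section 7 b (Structural brain adaptations) applies structural equation modelling to "Differences in connectivity between pre-test and post-test assessment, both within and between groups". It adds: "This analysis allows to investigate the causal relationships between brain structure and performance indicators while controlling for confounding factors". It lists nine factors to be accounted for: time since amputation, side and level of amputation, time using a prosthesis, previous prosthesis, age, sex, Mini-Mental State Examination score and education. The level is 5%.

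Section 7 b gives no arrow. The direction comes from H2 in section 5 d: "we expect that these disparities in brain structural connectivity will translate into a change in performance on the physical tests".

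The timing is in section 6.1 d:
- First scan: "At week 0, when initiating the rehabilitation, participants will undergo a baseline MRI-scan at the University hospital Brussels". Allocation to a foot follows.
- First performance test: "At the end of the rehabilitation, after 12 weeks, participants will perform baseline functional performance tests".
- After week 24: "participants will undergo the same MRI and functional performance tests as during the baseline assessments to evaluate the changes that occurred".

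Section 6.4 a agrees. At 12 weeks "the subject will be expected at Axiles Bionics for a series of non-invasive tests", with no visit to radiology. Section 6.1 e nevertheless speaks of MRI at pre-, mid- and post-test. Section 6.3 e states that allocation is non-randomised.

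**The concern.** A path coefficient fitted to observed covariances tests conditional association. Direction has to come from somewhere else: manipulation of the supposed cause, a time order that separates cause from effect, or a valid instrument. Section 7 b credits the analysis itself with access to causal relationships, and H2 relies on this to say that connectivity differences produce performance differences.

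Suppose that better walking alters connectivity, or that general recovery alters both. The model could still return a significant brain-to-performance path, and the trial could then report a neuroplastic mechanism for the device that its data do not distinguish from the alternatives.

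**Working it through.** The protocol gives no effect size, power or path diagram for this model, so there is no stated figure to reproduce. The check has three parts.

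**1. What could orient the path**
- *Manipulation:* none of brain structure.
- *Instrument:* prosthesis type is not randomly assigned. A foot can also change walking mechanically without acting through the brain.
- *Time order:* MRI is at weeks 0 and 24, function at weeks 12 and 24. Brain change is observable only over 0–24, performance change only over 12–24. The second interval lies inside the first, so no earlier brain change can be set against a later performance change. Performance is not measured before week 12.

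**2. A simple recursive path on the listed covariates**

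Inputs: N = 40 with amputation (section 7 e), or 40 × 0.9 = 36 after the planned 10% drop-out; 5% level, taken as two-sided; group plus nine factors, each entered as one term. The partial correlation r is not given; 0.3, 0.4 and 0.5 are assumed.

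With an intercept, the predictor and ten adjustment terms, df = N − 12, which is 28 at N = 40 and 24 at N = 36. The test statistic is

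t = r·√df / √(1 − r²).

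Because r is symmetric in brain and performance, regressing performance on brain and regressing brain on performance give the same t. For example, r = 0.4 and N = 40 give 0.4 × √28 / √0.84 = 2.31 either way. In simulation (8,000 runs per cell) the two t statistics never differed by more than 1e-13.

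Rejection rates for the brain-to-performance path:

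| N | r | brain drives performance | performance drives brain | common cause only |
|---|---|---|---|---|
| 40 | 0.3 | 37% | 37% | 37% |
| 40 | 0.4 | 60% | 61% | 61% |
| 40 | 0.5 | 83% | 82% | 83% |
| 36 | 0.3 | 32% | 32% | 33% |
| 36 | 0.4 | 54% | 54% | 54% |
| 36 | 0.5 | 77% | 77% | 77% |

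With no association the rate is 5%. Differences along a row are within simulation error of about one percentage point.

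**3. Paths on the actual visit schedule**

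N = 40, 8,000 runs, no covariates, assumed standardised path coefficient 0.5. Rejection when brain drives performance versus when performance drives brain:
- Performance change on brain change: 53% versus 52%.
- Week-24 performance on brain change, adjusted for week-12 performance: 56% versus 55%.
- Week-24 brain on week-12 performance, adjusted for week-0 brain: 51% versus 52%.
- Performance change on week-0 brain: about 5% in both cases.

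None of these paths separated the two directions.

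**The case against.** **Wording.** The protocol says the analysis allows causal relationships to be investigated; it does not say the model will reveal them. H2 is an expectation, and a hypothesis may be causal. Structural equation models can estimate causal parameters conditional on stated assumptions. This stands: it would go too far to call any causal use of the model invalid. But the protocol states no such assumptions, and the design supplies nothing to support them.

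**Unspecified model.** The exact equality holds for a single recursive path with one covariate set. The protocol does not fix that model, and a SAP might set out another. This also stands as a limit. However, a path diagram cannot supply missing time order or an instrument. A real mid-study MRI with cross-lagged paths could help; section 6.1 e mentions one, but sections 6.1 d and 6.4 a schedule none.

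**Adjustment and allocation.** Conditioning on the nine factors does not remove an unmeasured common cause, as the last column of the table shows. Sections 5 c and 7 e mention age strata and a block size, which might suggest randomisation. Section 6.3 e says otherwise, and random allocation of feet would still not randomise brain structure.

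**Stronger readings that the documents do not support.**
- A reader might infer that the protocol contradicts H2, because it cites a "study examining the effect of 12 weeks balance training in healthy and older adults on neuroplasticity". That citation justifies the length of the intervention period. Training that changes the brain is also compatible with H2, as the first step of a chain from intervention to brain to performance.
- A reader might take 37% to 83% as the chance of a false causal claim in this trial. They are only the power to detect an assumed correlation and say nothing about how likely reverse causation is.
- A reader might think that week-0 connectivity as a predictor restores the time order. That scan precedes allocation, so it cannot carry the prosthesis-related differences that H2 concerns.

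**Conclusion.** The point holds. Section 7 b credits the structural equation model with a property that this design does not give it, and H2's directed claim depends on that property. A significant path would show covariate-adjusted association only. In the simple recursive case, forward, reverse and common-cause truths are indistinguishable. The absolute rejection rates rest on assumed correlations, a two-sided 5% test and one term per factor; their equality across the three truths does not depend on the size of the correlation. It is exact only for that model class, but the scheduled visits offered no usable alternative among the paths tried.

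The consequence is confined to the interpretation of the secondary aim (RO.2). H2's main claim, that networks differ between prostheses, does not rest on the brain-to-performance arrow. Six-minute walk distance has its own mixed model and is unaffected.

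**What to change.** - **Section 7 b:** replace the causal sentence with: *estimates the covariate-adjusted association between change in connectivity and performance; direction cannot be inferred*. Specify the brain–performance link as a residual covariance (partial correlation). Alternatively, keep a directed path and report it as conditional on stated, untestable assumptions.
- **Section 5 d, H2:** say that the connectivity disparities will be associated with, rather than translate into, a change in performance.
- **Sections 6.1 d, 6.1 e and 6.4 a:** reconcile the mid-study MRI with the visit schedule.

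The cost is a few sentences and one line of model specification, with no new data and no change to sample size. The price is a weaker mechanistic claim for RO.2.
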